### Sample size

2.3

Our sample size calculation is based on selecting functional MRI changes as an exploratory mechanistic outcome measure, given their higher sensitivity than neuropsychological tests at the preclinical stage in SCD patients (Viviano and Damoiseaux, 2020). This approach differs from many previous cognitive intervention studies that have used neuropsychological test scores as primary outcomes. The target sample size is informed by prior neuroimaging studies in individuals with SCD, where changes in functional MRI parameters served as the primary outcomes (Bhome et al., 2018), while also considering feasibility constraints (Belleville et al., 2023). Accordingly, we plan to recruit 60 participants, with 30 individuals allocated to each group. To account for an anticipated attrition rate of approximately 20%, based on dropout rates reported in comparable longitudinal cognitive intervention studies in older adults (Cheng et al., 2024; Fernandez-Gamez et al., 2026), we will initially enroll 72 participants (36 per group), with the expectation that at least 60 will complete the study.

If neuropsychological test scores were used as the primary outcome, a substantially larger sample size would be required. An *a priori* power analysis was conducted using G*Power version 3.1.9.4 (Heinrich Heine University, Düsseldorf, Germany), based on a two-group comparison of continuous outcomes within the t-test family (“Means: Difference between two independent means”). Equal group allocation was assumed (N₂/N₁ = 1), and a one-tailed test was selected given the directional hypothesis that the intervention would improve outcomes. The anticipated standardized effect size was set at Cohen’s d = 0.18, derived from prior meta-analytic evidence indicating a small-to-moderate effect consistent with neuroimaging-based outcomes in SCD populations (Bhome et al., 2018). With a Type I error rate (*α*) of 0.05 and statistical power (1 − *β*) of 0.80, the estimated required sample size would be 383 participants per group (total *N* = 766; df = 764; actual power = 0.8006). Given the extensive multimodal assessments and longitudinal design of the present study, recruiting a sample of this magnitude is not feasible. Therefore, this study is designed as an exploratory, hypothesis-generating trial with a smaller sample size, aiming to provide preliminary effect estimates and inform future large-scale confirmatory studies.

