##### Statistical analysis

2.5.2.5

Statistical analyses will be conducted within the framework of the general linear model (GLM). For the primary clinical outcomes (e.g., subjective cognitive measures, neuropsychological test scores), a linear mixed-effects model will be used to handle the repeated-measures structure of the data throughout baseline, post-intervention, and follow-ups, with time, group, and group × time interaction as fixed effects, and subject as a random effect. This approach naturally accommodates missing data under the missing-at-random (MAR) assumption without requiring complete cases. The primary analysis will follow the intention-to-treat principle, including all randomized participants regardless of adherence or dropout, with missing values handled using multiple imputation based on baseline characteristics and available follow-up data. A per-protocol sensitivity analysis will also be conducted, restricted to participants who complete at least 80% of the intervention sessions. Covariates to be included in adjusted models will comprise age, sex, years of education, and baseline cognitive scores, selected *a priori* for their known associations with cognitive outcomes in SCD populations.

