For the neuroimaging analyses, task-related regressors will be convolved with the canonical hemodynamic response function, and motion parameters will be included as nuisance covariates. A high-pass filter of 128 s will be applied to remove low-frequency drift. At the single-subject level, voxel-wise GLM analyses will be performed to identify task-related activation patterns. Contrasts of interest (e.g., recitation versus resting baseline) will be evaluated using directional T-contrasts. At the group level, individual contrast maps will be entered into second-level random-effects models. Directional two-sample T-tests will be used for between-group comparisons, and conditions with similar activation patterns may be combined to enhance statistical power. Statistical significance will be set at *p* < 0.05, corrected for multiple comparisons using the false discovery rate (FDR) at the voxel level. For exploratory analyses, an uncorrected threshold of *p* < 0.001 may be applied. Extracted effect sizes from predefined ROIs will be further analyzed using Statistical Product and Service Solutions (SPSS). One-way analysis of variance will be used to assess condition-related differences, while Spearman’s rank-order correlation will evaluate associations between neural activation and clinical variables (e.g., years of education and Cognitive Reserve Index questionnaire (CRI-q) scores). Statistical significance will be defined as *p* < 0.05.

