Education does not only contribute to cognitive reserve but also modulates neural recruitment patterns during cognitive tasks. A study led by Sylvie Belleville demonstrated that individuals with higher educational attainment exhibited distinct activation patterns following cognitive training using the method of loci. Participants engaged in memory training for 1 h per day over three consecutive weeks. During memory retrieval tasks, individuals with higher education levels showed differential activation in the right middle and inferior temporal gyri (Brodmann areas 20, 21, and 37), regions associated with semantic processing and memory integration (Belleville et al., 2023). These findings suggest that education influences compensatory neural strategies and training-induced plasticity. Accordingly, years of education will be recorded in our cohort, and the CRI-q (Lin et al., 2025) will be administered to quantify reserve-related variables. Where sample size permits, subgroup analyses stratified by educational attainment will be conducted to examine differential intervention effects.

Beyond cognitive reserve mechanisms, the stress hypothesis provides an additional neurobiological framework. This model emphasizes dysregulation of the HPA axis. Chronic stress or maladaptive stress responses may lead to sustained glucocorticoid hypersecretion, downregulation of hippocampal glucocorticoid receptors, and impairment of the negative feedback loop regulating cortisol levels. Prolonged exposure to elevated glucocorticoids is associated with hippocampal neuronal loss and has been implicated in the pathogenesis of dementia (Fratiglioni et al., 2004). Through comprehensive biomarker profiling of blood samples, including metabolic and inflammatory markers, our study aims to explore whether structured memorization training may modulate systemic pathways related to stress regulation and neuroprotection.

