Consistent with the hypothesis-generating nature of this pilot research, study outcomes are organized within a predefined inferential hierarchy. The primary outcome is designated as the principal efficacy endpoint and will serve as the main basis for evaluating intervention-related effects. The secondary outcome is pre-specified *a priori*; however, given the limited sample size typical of pilot studies, findings will be interpreted as supportive and hypothesis-generating rather than definitive. EEG, gut microbiota, and metabolomic measures are designated as exploratory outcomes. These measures are not powered for confirmatory inference and are intended primarily to generate preliminary effect-size estimates and identify candidate biomarkers for future adequately powered confirmatory trials.

Based on these findings, we anticipate that the primary outcome of this pilot trial is intervention-induced change in resting-state fMRI activation within the left medial temporal region, encompassing the hippocampus and parahippocampal gyrus, from baseline (T0) to post-intervention assessment at 6 months (T1). Increased resting-state fMRI activation in the left medial temporal region following recitation training is interpreted as reflecting enhanced cognitive reserve — the brain’s capacity to sustain normal cognitive function despite underlying neurodegenerative burden — consistent with the compensatory scaffolding framework of cognitive aging (Reuter-Lorenz and Park, 2014). We anticipate that the intervention group will demonstrate significantly greater increase in left medial temporal region activation compared to controls, with the effect expected to be more pronounced in participants with lower educational attainment — consistent with a compensatory neural response in individuals with lower a priori cognitive reserve (Stern et al., 2020).

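### The predicted larger effect at lower education has no stated analysis that estimates it: the plan offers only conditional stratified subgroups, where one group-by-years-of-education term would do it

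*Protocol article*

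**What the plan says.** Section 3.3 (Anticipated outcomes) names the primary outcome as change in left medial temporal resting-state fMRI from baseline to 6 months. It predicts a greater increase than in controls, "with the effect expected to be more pronounced in participants with lower educational attainment".

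Section 3.1 holds the only stated analysis of differential effects by education: "Where sample size permits, subgroup analyses stratified by educational attainment will be conducted to examine differential intervention effects". It gives no cut-point, no threshold for when the sample is large enough, and no comparison between strata.

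Education or the group comparison appears in three other stated analyses, all in section 2.5.2.5:
- The mixed model for clinical outcomes is specified "with time, group, and group × time interaction as fixed effects". The adjustment list follows: "Covariates to be included in adjusted models will comprise age, sex, years of education, and baseline cognitive scores".
- For imaging, "Directional two-sample T-tests will be used for between-group comparisons". No education term is mentioned.
- A rank correlation "will evaluate associations between neural activation and clinical variables (e.g., years of education and Cognitive Reserve Index questionnaire (CRI-q) scores").

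On size, section 2.3 says "we plan to recruit 60 participants, with 30 individuals allocated to each group". Section 2.6 adds only that relevant covariates will be adjusted for.

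**The concern.** A prediction that an effect is larger at lower education is a statement about a difference between two effects. Results within each education stratum do not give that difference, its standard error or a test of it. The other stated analyses do not supply it either. An education main effect adjusts for level, a two-sample t-test averages over education, and a correlation of activation with years of education does not say whether the intervention effect varies with education.

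At stake is how the moderation result is read. With small strata, one significant and one non-significant result is a common chance pattern, and here it could look like the predicted one. Grouping a variable recorded in years also discards information. Because the sample-size condition has no threshold, the plan does not fix whether the analysis will be done at all. The pilot's stated purpose is to supply effect estimates for later trials. An interaction estimate can be carried forward in that way; a pair of subgroup results is much less useful.

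**Working it through.** **The plan's own figure.** Section 2.3 gives one power calculation: two-group t-test, d = 0.18, one-tailed α = 0.05, power 0.80, 383 per group. The exact noncentral t gives 383 per group with power 0.8006, so it reproduces. No calculation is given for education.

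**Inputs.** From the document: 60 participants, 30 per arm; α = 0.05; d = 0.18 as the only planning effect. Assumed here: an even split by education (15 per arm per stratum), 60 analysed, outcome SD 1, normally distributed education, and d = 0.5 and 0.8 as further illustrative effects. Tests are two-sided unless stated.

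**Standard errors, in SD units.**
- Overall effect: √(2/30) = 0.258.
- Effect within one stratum: √(2/15) = 0.365.
- Difference between strata: √(2/15 + 2/15) = √(4/15) = 0.516, so a 95% half-width of 1.96 × 0.516 = 1.01.

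**Power.** Noncentral t with n per arm, df = 2n − 2 and noncentrality d√(n/2). With p the power in one stratum and the same true effect in both, the chance that exactly one is significant is 2p(1 − p).

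| True d in both halves | Power overall (30 per arm) | Power per stratum, p (15 per arm) | Exactly one significant, 2p(1 − p) |
|---|---|---|---|
| 0.18 | 0.105 | 0.076 | 2 × 0.076 × 0.924 = 0.14 |
| 0.5 | 0.478 | 0.262 | 2 × 0.262 × 0.738 = 0.39 |
| 0.8 | 0.861 | 0.562 | 2 × 0.562 × 0.438 = 0.49 |

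The effect detectable with 80% power rises from 0.74 SD overall to 1.06 SD within a stratum. The specific pattern of low education significant and high education not has chance p(1 − p), which is 7%, 19% and 25% at the three effect sizes.

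The plan uses directional tests for imaging. One-sided, p is 0.122, 0.379 and 0.689, and 2p(1 − p) is 0.21, 0.47 and 0.43. The conclusion is unchanged.

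**Interaction test instead.** In 4,000 simulated trials with no moderation (d = 0, 0.5, 0.8), the continuous group-by-education term was significant in 5.3%, 4.6% and 4.2%.

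**Cost of splitting.** For normally distributed education, a median split keeps 2/π = 0.64 of the information on a linear moderation. That is equivalent to 60 × 0.64, or about 38 participants.

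**Power of the interaction at N = 60**, mean effect d = 0.5, simulated:

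| Moderation (SD per SD of education) | Effect 1 SD above mean education | Continuous term | Median-split interaction |
|---|---|---|---|
| 0.3 | 0.5 − 0.3 = 0.2 | 19% | 14% |
| 0.5 | 0.5 − 0.5 = 0 | 45% | 31% |
| 0.8 | 0.5 − 0.8 = −0.3 | 82% | 62% |

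The continuous term is better in each row. Power is high only when moderation is strong enough to reverse the effect at higher education.

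**The case against.** The strongest reply is that the plan never says subgroup p-values will be compared, or that education will be cut in two. The sentence sits in the discussion of a journal article, outside both statistics sections, and cut-points and interaction terms for an exploratory analysis are commonly left to an analysis plan. The hypotheses listed in section 3.1 do not mention education; the prediction is one clause in section 3.3. The study describes itself as exploratory.

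Much of this stands, and it limits the point:
- A reader might infer that moderation will be declared from one significant and one non-significant subgroup. The document does not say so. What it shows is that no stated analysis estimates the difference.
- A reader might infer that the sample-size condition allows the analysis to be dropped once results are seen. The wording refers to numbers of participants, which can be counted without outcome data, and section 2.1 keeps analysts blinded until the primary analysis is complete. What stands is that no threshold is fixed.
- A reader might infer that education is already in the relevant model. It is listed after the model for clinical outcomes. No stated fMRI model contains it.
- The 39% figure needs d = 0.5. At the plan's own d = 0.18 it is 14%.

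The reply does not remove the point, because the plan is not silent. It names a method for examining differential effects, and that method does not provide the quantity predicted. Section 3.3 also promises effect sizes with 95% confidence intervals, but in its paragraph on EEG and microbiota, and not for a contrast between education levels.

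**Conclusion.** The point holds in limited form. The plan predicts effect modification by education on its primary fMRI outcome, and the one analysis it states for this gives within-stratum results only. With an even split, each stratum could reliably detect only an effect of about 1.06 SD. Discordant significance under identical true effects would occur in about 14% to 49% of trials for d from 0.18 to 0.8, against about 5% false positives for an interaction test.

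The discordance rates rest on the planned 60, a roughly even split and the assumed common effect, and on no assumed size of moderation. The 64% and the interaction powers also assume normally distributed education and linear moderation, and the 64% applies if the split is at the median. The document gives none of these.

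A better analysis would not make this pilot able to settle the question: at moderation of 0.3 SD per SD, the gain is from 14% to 19% power. The reason to change is that the predicted quantity would then be estimated, with its uncertainty shown. The main group comparison is unaffected.

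**What to change.** Replace the subgroup sentence in section 3.1 with one pre-specified analysis, labelled exploratory: a group × years-of-education term, with education continuous and its main effect included, in the model for baseline-to-6-month change in the left medial temporal ROI. If a repeated-measures mixed model is used, the term needed is group × time × education with its lower-order terms, because group × education alone would not isolate moderation of change.

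Report the estimate with a 95% CI, and model-based intervention effects at a low and a high number of years of education named in advance. Keep any stratum results as descriptive display. Drop the sample-size condition, since every analysed participant contributes to the term.

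The cost is small. Years of education is already collected at baseline (section 2.5.1), so no new data are needed, but an education-containing model for the ROI outcome has to be written down. There are two modest downsides: a single linear term can miss non-linear moderation, and the estimate will be imprecise at N = 60, so it should be presented as an estimate for later trials and not as a confirmatory test.

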### Strengths and limitations

3.2

A major strength of this study lies in its focus on a Chinese-speaking population, which remains underrepresented in longitudinal cognitive training research. By integrating multimodal assessments and long-term follow-up, this study aims to provide novel insights into the trajectory of SCD and the potential disease-modifying effects of sustained cognitive training within this population.

Several limitations should be acknowledged. First, recruitment may be challenging, as individuals with SCD often present with mild symptoms and may not seek medical attention in outpatient settings. Second, the comprehensive pre- and post-intervention assessments are time-intensive and may reduce participant willingness and adherence. Third, participants may be aware of whether they are assigned to the intervention or control group because of the use of a non-active control group, which may introduce performance and expectancy biases. Additionally, the use of a mobile application for training may pose usability challenges for older adults, potentially contributing to dropout.

To mitigate these limitations, participants will be recruited from both Neurology and Psychiatry departments, as well as through collaborations with community activity centers to enhance outreach. To improve adherence, only individuals willing to complete study assessments will be enrolled, and the training platform will be optimized for elderly users (e.g., larger Chinese characters and simplified interface design). Adherence will be operationally delineated as the completion of no less than 80% of the designated intervention, specifically including attendance at a minimum of 80% of scheduled training sessions and the fulfillment of at least 80% of the assigned daily practice throughout the six-month duration. Adherence will be monitored continuously throughout the trial using automated session logs recorded in the mobile application, and any participant who falls below the threshold will be flagged for follow-up by the research team. Reasons for non-adherence and dropout will be systematically documented to inform the interpretation of findings and the design of future trials.

To address expectancy-related bias, the present study acknowledges that participants in the intervention group may attribute cognitive improvements to the mere receipt of a structured program rather than to its specific active components — a cognitive placebo effect that cannot be fully disentangled from true intervention effects in the absence of an active control condition. We therefore incorporate validated credibility and expectancy questionnaires administered at baseline and post-intervention to enable statistical adjustment for potential influences on outcomes. Participant expectancy will also be assessed at enrollment to characterize the degree to which anticipation of benefit may have influenced self-reported outcomes. Future definitive clinical trials should employ an active control condition that matches the intervention in time, attention, and participant engagement to better isolate the specific effects of the intervention and reduce the risk of biases.

The risk of cross-group contamination should also be acknowledged. As participants are recruited from overlapping settings — including outpatient departments and community centers — individuals assigned to the control group may become aware of the intervention content through social interaction with participants in the intervention group. This could attenuate between-group differences and lead to an underestimation of true intervention effects. To minimize this risk, participants will be reminded at enrollment and throughout the trial not to discuss study procedures with others. Future trials should consider cluster randomization or geographically separated recruitment sites to further reduce the risk of contamination.

The cultural and linguistic specificity of the intervention represents an additional limitation. The cognitive training program incorporates Traditional Chinese poetry recitation, a practice deeply embedded in Taiwanese cultural and educational traditions. The cognitive demands, memorability, and emotional engagement associated with this material may not translate equivalently to populations with different linguistic backgrounds or cultural relationships to classical literary forms. Accordingly, the generalizability of findings to non-Chinese-speaking populations may be limited. Adaptation and revalidation of the intervention content are required before international replication.

Given the modest sample size, statistical power may be limited. If interim analyses indicate insufficient statistical power, additional participants may be recruited. Conversely, if statistically significant results are observed earlier than anticipated, early termination of recruitment may be considered.

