The study is designed as a randomized, assessor-blinded, controlled pilot study. A stratified block randomization sequence will be generated by an independent statistician using computer-generated random numbers, with stratification by age and sex to ensure balanced group allocation. Block sizes will be randomly varied to prevent predicting upcoming assignments. Allocation concealment will be ensured using the Sequentially Numbered, Opaque, Sealed Envelopes method; envelopes will be prepared and safeguarded by personnel not involved in recruitment, eligibility assessment, or intervention delivery. After eligibility assessment and informed consent are completed, a designated research assistant — otherwise uninvolved in outcome assessment — will open the envelope to reveal group assignment. Prior to allocation disclosure, all research personnel will remain blinded to the randomization sequence. Given that the intervention is behavioral in nature, complete blinding of participants and interventionists is not feasible. However, several measures will be implemented to minimize performance bias. Participants will be instructed not to discuss their group assignment with outcome assessors. Interventionists will have no role in outcome measurement or data analysis. Outcome assessors — including neuropsychological evaluators (psychologists) and radiologic technologists — will be formally blinded to group allocation throughout the trial and will be kept separate from the intervention team. To maintain blinding integrity, assessors will be reminded of their blinded status at each assessment visit, and any unblinding events will be documented and reported. Data analysts will similarly remain blinded to group assignment until the primary analysis is complete. The inherent risk of performance bias arising from participant awareness of group assignment will be mitigated by standardizing intervention protocols, using objective outcome measures where possible, and monitoring for differential dropout between groups.

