### Statistical methods

2.6

The primary efficacy analysis will be conducted using generalized linear mixed-effects models to analyze repeated measures data, with adjustment for relevant covariates. Microbiome analyses will be performed using DESeq2 to identify differentially abundant taxa and linear discriminant analysis effect size to detect potential microbial biomarkers. Metabolomic data will be analyzed using partial least squares discriminant analysis, and pathway enrichment analysis will be conducted using the MetaboAnalyst platform. Multi-omics integration will be performed using Spearman correlation-based network analysis and causal mediation analysis to investigate regulatory mechanisms along the gut-brain axis. Multiple comparisons will be corrected using FDR, with a threshold of *q* < 0.05. All statistical analyses will be conducted using R (version 4.4.0; R Core Team, 2024) and SPSS (version 29.0; IBM Corp., Armonk, NY, USA), with statistical significance set at *p* < 0.05.

Given the inherent complexity and multi-layered nature of multi-omics data, if the aforementioned methods are insufficient for comprehensive analysis, we will collaborate with the institutional Artificial Intelligence Center affiliated in our hospital to implement advanced analytical approaches. These may include machine learning, network-based modeling, and partial least squares regression, among others, to construct predictive models that characterize causal or associative relationships between biological markers and clinical outcomes (e.g., cognitive function and depression). The predictive performance of different models will be systematically compared.

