#### Sponsorship and oversight

2.7.1

The trial is sponsored by the China Medical University Hospital. The sponsors and funders have no role in the study design, data collection, management, analysis, or interpretation. A Steering Committee, composed of senior researchers in neuroscience and clinical neurology, oversees trial progress. An independent Data Management Team at China Medical University Hospital handles data auditing. A formal Data Monitoring Committee was not deemed necessary due to the non-invasive nature of the behavioral intervention in this trial. No formal interim efficacy analysis was planned, and early stopping for efficacy was not considered applicable. However, safety is monitored by the Steering Committee, whereas trial conduct is monitored quarterly by the Research Ethics Committee.

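### Section 3.2 lets recruitment stop on early significance or extend after an interim look, while section 2.7.1 says neither applies, and no error control covers the looks

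*Protocol article*

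**What the plan says.** Section 2.7.1 (Sponsorship and oversight): "No formal interim efficacy analysis was planned, and early stopping for efficacy was not considered applicable". The same section explains the absence of a monitoring committee: "A formal Data Monitoring Committee was not deemed necessary due to the non-invasive nature of the behavioral intervention in this trial".

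Section 3.2 (Strengths and limitations), in a short paragraph on limited power, says the opposite in two sentences. The first allows the sample to grow: "If interim analyses indicate insufficient statistical power, additional participants may be recruited". The second allows it to shrink: "if statistically significant results are observed earlier than anticipated, early termination of recruitment may be considered".

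Three other places bear on this:

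- Section 2.6 (Statistical methods) gives the error control: "Multiple comparisons will be corrected using FDR, with a threshold of *q* < 0.05", and "with statistical significance set at *p* < 0.05".
- Section 2.1 (Aims, study design, and settings) says: "Data analysts will similarly remain blinded to group assignment until the primary analysis is complete". Section 2.7.3 limits unblinding to medical emergencies.
- Section 2.3 (Sample size) plans 60 participants, 30 per group, from 72 enrolled.

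**The concern.** Ending recruitment because the results are significant is early stopping for efficacy, which section 2.7.1 says does not apply. An analysis plan cannot follow both sections.

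Together, the two sentences of section 3.2 make the final sample size depend on the observed result in both directions: stop if it is significant, carry on or extend if it is not. If every look is tested at 0.05, the chance of at least one false positive exceeds 0.05. Correction across outcomes does not repair this, because it handles many tests at one time and not one test repeated over time.

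The second consequence matters more for a pilot. The stated aim is to supply effect sizes for a definitive trial. An estimate taken at the moment it first crosses a significance threshold is biased upward, and a later trial sized on it would be too small. Section 3.3 also names a principal efficacy endpoint as the main basis for judging the intervention, so a false positive has a place to land.

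A between-group look during recruitment would also put pressure on the blinding rules in sections 2.1 and 2.7.3, and there is no monitoring committee to keep the result from those running the trial.

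**Working it through.** **The plan's own figure.** Section 2.3 gives 383 per group for a one-sided two-sample t-test with d = 0.18, α = 0.05 and power 0.80. The noncentral t distribution gives 383 per group and power 0.8006, an exact match. The concern does not depend on this figure, but it shows how easily the extension clause could be triggered. At 30 per group and d = 0.18 the same formula gives power of 17% one-sided or 11% two-sided.

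**Inputs for the error rate.** From the documents: planned total of 60, 1:1 allocation, significance at 0.05. Section 2.3 uses a one-tailed test ("a one-tailed test was selected given the directional hypothesis that the intervention would improve outcomes") and section 2.6 states no side, so both are shown. Assumed, because the documents do not say: the number and timing of looks, and the size of any extension.

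**Method.** Under no effect, the test statistics at cumulative sample sizes n₁ < n₂ < … are jointly normal, with correlation √(nᵢ/nⱼ) for nᵢ < nⱼ. The false-positive rate is 1 − P(no statistic crosses the critical value c at any look), with c = 1.960 two-sided or 1.645 one-sided. For looks at 30 and 60 the correlation is √(30/60) = 0.707.

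| Assumed looks (total N) | Two-sided | One-sided |
|---|---|---|
| 60 only, as section 2.7.1 implies | 5.0% | 5.0% |
| 30, 60 | 8.3% | 8.0% |
| 60, then 90 if not significant | 7.7% | 7.4% |
| 60, then 120 if not significant | 8.3% | 8.0% |
| 30, 60, 90 | 10.7% | 10.1% |
| 30, 60, 120 | 11.3% | 10.7% |
| 30, 60, 90, 120 | 12.6% | 11.7% |

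**Effect of overrun.** The table counts the first crossing as the final result. Section 3.2 speaks of ending recruitment, and the primary outcome is change to 6 months (section 3.3), so people already enrolled at a look would still provide data. Simulating 2,000,000 null trials with a look at 30 and otherwise a final test at 60:

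- If a stop at 30 is finally tested on 45 people, the rate is 5.6% two-sided and 5.6% one-sided.
- If all 60 are already enrolled, it is 5.0% and 5.0%.
- With the overrun to 45 and also an extension to 90 when the test at 60 is not significant, it is 8.0% and 7.7%.

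**Effect-size bias.** At a look with 30 analysed (15 per group, 28 degrees of freedom), the smallest observed d that is significant is t × √(2/15):

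- one-sided: 1.701 × 0.365 = 0.62
- two-sided: 2.048 × 0.365 = 0.75

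The protocol's anticipated d is 0.18. An estimate reported from such a stop is therefore at least 0.62/0.18 = 3.4 times (one-sided) or 0.75/0.18 = 4.2 times (two-sided) that value.

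**The case against.** Several points can fairly be made for the plan.

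- Section 2.7.1 denies only a formal interim analysis, and section 3.2 is a loosely worded contingency in the discussion. This softens the tone but does not remove the conflict. The clause on early stopping carries no such qualifier, and informal looks are harder to control than formal ones.
- The figures assume no overrun. This stands. For the early stop alone, the inflation can shrink to almost nothing if many participants are already enrolled at the look. The extension route is unaffected: it still gives about 7.5% to 8%.
- Low power could be judged from the pooled standard deviation and attrition, without comparing groups. This is possible, and such a rule would be harmless, but the sentence does not say so.
- A comparison under masked group codes need not unblind the analyst. This also stands, so the blinding point is conditional and only supporting. The result would still reach those deciding on recruitment.
- Boundaries and look schedules usually belong in an analysis plan. Their absence alone would be no finding. The fault is that the article introduces data-dependent stopping and extension while denying that any interim efficacy analysis is planned.
- The trial is an exploratory pilot, so no confirmatory claim rests on the error rate. The argument has limited force, because stopping on significance damages the effect estimates that are the pilot's purpose.

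**Conclusion.** The concern holds. Sections 2.7.1 and 3.2 contradict each other on whether the trial can stop early or change size on interim results, and following section 3.2 at an unadjusted 0.05 raises the false-positive rate. Under the assumed schedules with no overrun, it lies between about 7.4% and 12.6%. With overrun and no extension it can fall back towards 5%. These figures rest on assumed looks and equal information per participant. The upward bias applies to any estimate reported because it crossed a threshold. This should be corrected before any look at the data, since the damage cannot be undone afterwards.

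**What to change.** Delete the two sentences in section 3.2 and let section 2.7.1 stand: a fixed sample size, and one between-group analysis after the last 6-month (T1) visit.

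If flexibility in sample size is wanted, replace the first sentence with a blinded re-estimation rule. It should use only the pooled standard deviation and overall attrition, make no between-group comparison, and state a maximum sample size.

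If the sponsor instead wants a genuine early stop, section 2.7.1 must be rewritten to fix the looks, the boundary, and who sees the results. As an illustration, one look at half the information with overall two-sided 0.05 needs nominal thresholds of 0.0294 at both looks (Pocock), or 0.0052 then 0.0480 (O'Brien-Fleming). This controls the error rate but not the bias in the estimate, so it suits this pilot less well.

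The recommended change costs two sentences of wording. What is lost is an informal option to stop early, which a pilot meant for estimation does not need.
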